### Data management and monitoring

Patient flow in the participating centres will be organised using a secured tailor-made Access database. The decoding list will be kept in the Investigator Site File in a secured place in the dialysis department. Data-entry will be coded and entered in Castor [43]. Range limitations will be build into Castor to prevent misclassification and measurement error. Research assistants will be trained in data collection and data entry to enhance data quality.

The risk of this trial is classified as ‘negligible’ and a study specific monitoring plan is created in close corporation with the data monitoring committee which includes double data entry checks. If deemed necessary by the monitoring committee, monitoring can be intensified. No adverse events are to be expected specifically related to this intervention. Actively suicidal participants will be excluded from the trial as described above.

### Sample size

The power calculation is based on the comparison between T1 to T0 between the intervention and the control group. We took the conservative small to medium effect size (Cohen’s d = 0.4) on the primary outcome measure, while using a power 0.80, with alpha set on .05. Therefore, a total set of *N* = 99 patients is required in each arm. The design effect of cluster-randomization is estimated to be 1.04. After adjustment for cluster randomization, sample size is calculated to be *N* = 206 in total (103 per arm).

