**Methods:**

This study is a cluster randomized controlled trial (RCT) that investigates the effectiveness of a 5-week Internet-based self-help Problem Solving Therapy (PST) for depressive symptoms in dialysis patients. Depressive symptoms will be measured using the Beck Depression Inventory – second edition (BDI-II), with a cut-off score of ≥10. We aim to include 206 dialysis patients with depressive symptoms who will be cluster randomized to the intervention or the Care as Usual (CAU) control group. Secondary outcomes will include anxiety symptoms, quality of life, economic costs and clinical outcomes, such as inflammatory factors and hair cortisol levels. Assessments will take place at baseline (T0), 2 weeks after intervention (T1) and 6 months (T2), 12 months (T3) and 18 months (T4) after intervention. The control group will be measured at the same time points. Analysis will be based on the intention-to-treat principle. Mixed models will be used to assess the changes within each condition between pre-treatment and post-treatment.

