## Discussion

There is a need for adequately powered RCT’s to assess the effectiveness of treatment options for depressive symptoms in dialysis patients, as evidence is currently lacking. In order to conduct a high-quality trial, a multidisciplinary team with various experts related to dialysis and depression was involved in the development of the intervention and the study design. This trial may provide insights on the effectiveness, feasibility and applicability of Internet-based self-help PST in the dialysis population.

This study has several limitations. First, the intervention may not be applicable for patients with cognitive impairment, illiteracy, other cultural background or insufficient Dutch language skills. Second, Internet-based treatment on tablet-computers might not be suitable for dialysis patients who are not familiar with the Internet or tablet-use, or who suffer from vascular disease related problems such as impaired vision or polyneuropathy of their hands. Both of these problems will be solved by offering assistance by the study team during the intervention which will be documented, furthermore patients can be provided with a printed version of the intervention. Third, drop-out rates are high for internet-based self-help interventions in other populations [29, 30], to cope with this problem we embed the intervention in routine care in the dialysis departments during dialysis treatment with frequent face-to-face interaction with the participants, which will make it easier to prevent early termination. Furthermore, we aim to provide insight in the reasons for termination or non-participation in this study.

If demonstrated to be (cost) effective, Internet-based PST offers new possibilities to treat many dialysis patients with symptoms of depression and to improve the quality of care. This RCT is aimed at contributing to better recognition and adequate treatment of symptoms of depression in dialysis patients in the future.

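### The 206 patients to be included equal the number that must be analysed at T1 for 80% power, so on the stated basis the 0.80 holds only if no T1 score is lost

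*Protocol article*

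**What the plan says.** All places are in the protocol article.

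- **Sample size**, comparison powered: "The power calculation is based on the comparison between T1 to T0 between the intervention and the control group".
- **Sample size**, inputs: "We took the conservative small to medium effect size" (Cohen's d = 0.4), "while using a power 0.80, with alpha set on .05", giving 99 patients per arm before clustering.
- **Sample size**, last step: "The design effect of cluster-randomization is estimated to be 1.04. After adjustment for cluster randomization, sample size is calculated to be" 206 in total, 103 per arm. No further factor follows.
- **Abstract, Methods**: "We aim to include 206 dialysis patients with depressive symptoms", and these are the patients who are then randomised.
- **Statistical analysis**: intention to treat; mixed models with cluster, centre and baseline score; multiple imputation depending on the type of missing data. Missing data are therefore expected in principle.
- **Intervention**: a patient found to be actively suicidal while working through the modules is excluded from the study. This occurs after randomisation.
- **Discussion**, limitations: "drop-out rates are high for internet-based self-help interventions in other populations". The response is to embed the intervention in dialysis sessions so that early stopping is easier to prevent. The sample size is not mentioned.

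**The concern.** A sample-size formula returns the number of patients who must contribute an outcome. Here that number and the recruitment target are the same, so the power claim carries an unstated assumption of complete T1 follow-up. Other parts of the article do not make that assumption.

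The point matters because the Background and Discussion present the trial as supplying the adequately powered RCT that is so far lacking in this population. A null result would be read in that light. If the chance of missing d = 0.4 is closer to 29% than 20% (the figure at an assumed 20% loss, unadjusted), readers should know it.

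**Working it through.** **Inputs from the Sample size section:** d = 0.4, power 0.80, alpha 0.05, design effect 1.04. Sidedness is not stated; a two-sided test reproduces the 99, while a one-sided test gives 78.

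**1. Reproduce the plan's figure.**
- n per arm = 2 × (1.96 + 0.8416)² / 0.4² = 98.1, rounded up to 99.
- 99 × 1.04 = 102.96, rounded up to 103 per arm; 2 × 103 = 206. The stated figure is reproduced.

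**2. Look for a reserve.**
- 103 / 1.04 = 99.04 effective patients per arm. Power at d = 0.4 is 0.800 by the t-test (0.804 by the normal approximation). There is no slack.
- The Randomization section's 72 clusters of about 3 patients would make 216, but 206 / 72 = 2.86, which rounds to 3. This is not a hidden margin.

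**3. Power with 206 randomised and a fraction m lost at T1.** Effective n per arm = 103 × (1 − m) / 1.04. The documents give no m, so the range is an assumption.

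| T1 loss m | Analysed | Effective n per arm | Power at d = 0.4 | d detectable with 80% power |
|---|---|---|---|---|
| 0% | 206 | 99.0 | 0.80 | 0.40 |
| 5% | 196 | 94.1 | 0.78 | 0.41 |
| 10% | 185 | 89.1 | 0.76 | 0.42 |
| 20% | 165 | 79.2 | 0.71 | 0.45 |
| 30% | 144 | 69.3 | 0.65 | 0.48 |

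The t-test and the normal approximation agree to two decimals on power at every non-zero loss shown. A design effect of 1.04 with clusters of 3 implies an ICC of 0.04 / (3 − 1) = 0.02. Letting the design effect shrink as clusters lose patients changes power by less than one percentage point.

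**4. What baseline adjustment could recover at 20% loss.** Let r be the baseline–T1 correlation, also an assumption.
- *d scaled to the raw-score SD:* effective n becomes 79.23 / (1 − r²).
  - r = 0.4: 94.3, power 0.78
  - r = 0.5: 105.6, power 0.82
  - r = 0.6: 123.8, power 0.88
- *d scaled to the change-score SD:* the effect relative to the adjusted residual SD becomes 0.4 × √(2 / (1 + r)).
  - r = 0.4: 0.478, power 0.85
  - r = 0.5: 0.462, power 0.82
  - r = 0.6: 0.447, power 0.80

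On the raw-score scale, a correlation of about 0.32 offsets 10% loss and about 0.45 offsets 20%.

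**The case against.** The strongest reply is that the planned analysis is more efficient than the calculation. With baseline score in the model, a moderate correlation restores 0.80 or more even at 20% loss. This stands as a possibility, and it means that the trial has not been shown to be underpowered. It does not rescue the stated figure: the Sample size section gives no correlation, takes no credit for adjustment, and does not say which SD scales d.

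Other replies have partial force.

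- *The Discussion predicts high drop-out in this trial.* A reader might infer this, but the text does not support it. The sentence concerns other populations and, in context, stopping the intervention. A patient who abandons the modules but completes the BDI-II at T1 stays in the intention-to-treat analysis. T1 falls within two weeks of the intervention, on paper questionnaires handed out at dialysis, so T1 loss may be modest.
- *Stopping the modules dilutes the effect as well.* A reader might add a further reduction in d. The documents give no size for it, and they call 0.4 conservative without saying that it is an effect in completers. No such reduction is used here.
- *Safety exclusions add up across several sections.* Only the Intervention section clearly describes an exclusion after randomisation. The one under Exclusion criteria is a matter of eligibility, and the data-monitoring section merely refers back. No frequency is given.
- *Later BDI-II scores and imputation help.* Patients who miss T1 but return at T2 to T4 can contribute some information through the mixed model. The table may therefore somewhat overstate the loss, but neither route fully replaces missing T1 scores.
- *A journal article condenses the protocol.* This does not explain the point. Every step from 99 to 206 is printed, and an allowance for loss applied elsewhere could not leave the same 206 as both the analysed and the included number.

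**Conclusion.** The arithmetic in the article is correct. The fault is that its result, a number to be analysed, is also used as the number to be included. On the stated basis the 0.80 is true only at zero T1 loss. The shortfall is about 2 percentage points at 5% loss, 4 at 10%, 9 at 20% and 15 at 30%. These rest on an assumed loss range, a two-sided test, a design effect of 1.04 and no credit for baseline adjustment or later visits.

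A reader might go further and conclude that the trial will not deliver 80% power. The documents do not support that: they give no T1 loss rate, and the planned model could make up the difference. What is established is that the claimed power cannot be verified from the calculation given. This calls for a corrected statement of power; it is not a reason to change the design.

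**What to change.** Rewrite the Sample size paragraph, without enrolling more patients:

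1. Say that 206 is the number randomised.
2. Give an expected proportion without a T1 BDI-II, with its basis. Enrolment began in January 2018, so T1 completion to date, pooled over arms, could serve. A rate should not be inserted without a source.
3. Restate power, or the d detectable with 80% power, for 206 randomised, in one of two ways:
   - unadjusted, using 103 × (1 − loss) / 1.04 per arm; for illustration only, 20% loss would read as 165 analysed, power 0.71, or 80% power for d = 0.45; or
   - for the planned baseline-adjusted model, stating the baseline–T1 correlation, the SD that scales d, and the design effect (1.04, or an ICC of 0.02 with clusters of 3).

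The cost is one paragraph. The stated power may look slightly less favourable, or may be confirmed if the correlation is high enough. Recruitment, randomisation and analysis do not change.

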### Statistical analysis

We will quantify the flow of participants through the study using frequencies and percentages in accordance with the SPIRIT flow diagram shown in Fig. 1. Missing data will be reported and discussed in the manuscripts on the trial. Depending on the type of missing data, multiple imputation will be used to handle missing data. Descriptive statistics will be used to describe non-consent, treatment adherence and completion, drop-out and exclusion. The main analysis to assess the effectiveness of the intervention will test differences in the change in depression scores pre-and post-treatment between the intervention and control arms. Analysis will be done per intention to treat principle. Differences in change in depressive symptoms and other continuous secondary outcomes between intervention and control will be assessed using mixed models with the respective clusters, centres and baseline scores as covariates. The analyst will be blinded to the treatment group allocation. Treatment effect over time will be tested by adding a group*time interaction term into the model. Regression models will be used to explore (biochemical) mechanisms. Multivariable adjustment will be done deliberately within the causal pathway in order to explain potential mechanisms.

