### Randomization

Cluster randomisation will be applied to reduce possible contamination between both arms of the trial. Participants will be cluster-randomized in a 1:1 allocation to the intervention or CAU after baseline measurements (T0). Clusters will be based on the shift of the dialysis session per dialysis centre. The average dialysis centre has 4 major shifts: Monday morning, Monday afternoon, Tuesday morning and Tuesday afternoon. A total of 72 clusters of average 3 patients in 18 participating dialysis centres will be present in our study. Clusters will be randomized using stratified blocks per participating dialysis centre.

Randomization will be performed and registered by an automated computer software programme to ensure independent allocation. Baseline measurements will be completed prior to randomization. The coordinating researcher assigns the intervention to participants. Although the treating nephrologist will not be actively informed about the depression score and allocation, we do not consider them blinded as patients and investigators will not be blinded. Outcome assessors are blinded and data analysts will be blinded until primary analysis will be performed.

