The intervention consists of five modules with explanatory text, animations, figures and exercises and is called ‘Worry Less for Dialysis Patients’ (in Dutch: “Minder Zorgen voor Dialyse Patiënten”). Patients are requested to complete 1 session each week and to finish the module within 6 weeks. However, there will be a possibility to extend this period up to 10 weeks, which will be documented. Patients are offered to complete the sessions on a tablet computer provided by this trial during dialysis sessions, but if preferred it can also be done from home on a private tablet or computer. If patients are unfamiliar with tablet computers, they are offered the opportunity to receive a printed booklet of the intervention. If patients have problems with the use of the tablet due to unfamiliarity, physical limitations, shunt use in the dominant arm of Dutch writing problems, they will be supported by a member of the research team, which will be documented. Supported care within the module is provided by a trained therapist and consists of weekly online feedback on their assignments. Patients have the possibility to request their therapist for additional support via the website. Treatment non-adherence and drop-outs will be discussed with the patients. Reasons for not completing the modules and patient satisfaction will be obtained via a short evaluation questionnaire. If a patient expresses suicidal ideations in the assignments of the intervention, suicide risk will be assessed over telephone by the supporting therapist under supervision of a psychiatrist. If the patient is actively suicidal, the patient will be excluded from the study and the attending nephrologist will be informed and advised to refer the patient for adequate safety and treatment.

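### Neither the primary model nor the 1.04 design effect carries clustering by therapist in the treated arm; with several therapists and a positive therapist correlation the standard error is too small

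*Protocol article*

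**What the plan says.** All references are to the protocol article.

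- **Guidance.** Under Study design and Intervention, a trained therapist gives each treated patient individual feedback every week through the online portal. In addition, "Patients have the possibility to request their therapist for additional support via the website". Some patients may work from a printed booklet.
- **Control.** Control patients do not receive the Internet-based therapy, so they have no study therapist.
- **Randomization.** Patients are "cluster-randomized in a 1:1 allocation to the intervention or CAU". A cluster is a dialysis shift within a centre: 72 clusters averaging 3 patients in 18 centres, stratified by centre.
- **Statistical analysis.** The primary comparison uses "mixed models with the respective clusters, centres and baseline scores as covariates".
- **Sample size.** The assumed effect is given as: "We took the conservative small to medium effect size (Cohen’s d = 0.4) on the primary outcome measure". With 80% power and a 5% alpha this leads to 99 per arm. On clustering the section says: "The design effect of cluster-randomization is estimated to be 1.04". The result is 206 patients, 103 per arm.
- **Blinding.** Randomization says that data analysts stay blinded until the primary analysis has been performed. Statistical analysis repeats that the analyst is blinded to allocation.

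The article does not give the number of therapists, how patients are assigned to them, or a therapist ICC.

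**The concern.** Treated patients who share a therapist may also share that therapist's skill and style, so their outcomes can be correlated. This can happen in the intervention arm only, which makes the design partially nested. Because the feedback is online, a therapist may serve many shifts and centres, and shift and centre terms need not absorb the correlation. The article names the levels that its model covers and the clustering that its sample size covers, and therapists are in neither list.

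If the correlation is there and is ignored, the confidence interval for the primary effect is too narrow, the type I error exceeds 5%, and 103 per arm carries less information than the calculation assumes. The caseload matters too. The plan enlarged the trial for a 4% variance inflation from groups of about 3, whereas a therapist's caseload would be about 10 with 10 therapists and about 21 with 5.

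**Working it through.** **1. The plan's own figure.** Inputs from Sample size: d = 0.4, alpha 0.05 (two-sided reproduces the figure; one-sided would give 78 per arm), power 0.80. This gives 99 per arm. 99 × 1.04 = 102.96, so 103 per arm and 206 in total. Variance of the difference in SD units: 2 × 1.04/103 = 0.02019, so SE = 0.1421. Power = Φ(0.4/0.1421 − 1.96) = 0.804. The stated figure holds on its own terms.

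**2. What the 1.04 covers.** With an average of 3 per shift, 1 + (3 − 1) × ICC = 1.04 gives a shift ICC of 0.02. The 1.04 is therefore fully explained by shifts.

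**3. Adding therapists to the treated arm.** Assume k therapists with equal caseloads of 103/k and a therapist ICC ρ. Both k and ρ are assumptions.

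- Variance = [2 × 1.04 + (103/k − 1) × ρ]/103
- SE ratio = √{[2.08 + (103/k − 1) × ρ]/2.08}
- Power with a correct SE = Φ(0.4/SE − 1.96)
- Type I error if therapists are ignored = 2 × [1 − Φ(1.96/SE ratio)]

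Worked case, k = 5 and ρ = 0.02: (20.6 − 1) × 0.02 = 0.392. SE ratio = √(2.472/2.08) = 1.090. SE = √(2.472/103) = 0.1549. Power = Φ(2.582 − 1.96) = 0.733. Type I error = 2 × [1 − Φ(1.798)] = 7.2%.

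| Therapists | ICC | SE ratio | Power, correct SE | Type I error, therapists ignored |
|---|---|---|---|---|
| any | 0 | 1.000 | 0.804 | 5.0% |
| 10 | 0.01 | 1.022 | 0.786 | 5.5% |
| 10 | 0.02 | 1.044 | 0.769 | 6.0% |
| 10 | 0.05 | 1.106 | 0.721 | 7.6% |
| 5 | 0.01 | 1.046 | 0.768 | 6.1% |
| 5 | 0.02 | 1.090 | 0.733 | 7.2% |
| 5 | 0.05 | 1.213 | 0.641 | 10.6% |
| 3 | 0.02 | 1.149 | 0.688 | 8.8% |

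The added variance is 0.093/2.08 = 4.5% for 10 therapists at 0.01, 0.186/2.08 = 8.9% for 10 at 0.02, and 0.392/2.08 = 18.8% for 5 at 0.02.

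**4. Do shift and centre terms absorb it?** A simulation used 18 centres, 4 shifts each, 3 patients per shift and a shift ICC of 0.02. It was analysed on shift means with centre effects, without a baseline covariate and without a therapist term. Type I error was 5.0-5.4% at therapist ICC zero, 7.0-7.5% for 5 therapists at 0.02, 10.3-10.9% for 5 at 0.05, and 5.9% for 10 at 0.02. The ranges span assignment of therapists by patient, by shift and by centre. In none of these did the shift and centre terms remove the effect.

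**5. Baseline adjustment.** The sample size takes no explicit credit for the baseline covariate. Suppose that d is in post-score SDs and the baseline correlation is 0.5 (assumed), so that variance is multiplied by 1 − 0.5² = 0.75. Power is then 0.90 without therapists. With 5 therapists at 0.02 it is 0.85 if the therapist component shrinks as well. A baseline score taken before therapy would not generally shrink that component. If the component is left whole, the variance is (0.75 × 2.08 + 0.392)/103 = 0.01895, SE 0.1377, and power Φ(2.906 − 1.96) = 0.83. The SE ratio is then √(1.952/1.56) = 1.119, larger than 1.090. Baseline adjustment may restore power, but it does not correct the standard error.

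**The case against.** **A journal article condenses its sources.** A treated-arm random effect and its degrees of freedom are typical of an analysis plan that is not shown, and nothing in the article excludes a further term. This limits the point but does not remove it: the article states which levels the model contains and what the 1.04 is for, and both lists stop short of the therapist.

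**A reader might infer that the standard error is too small as a matter of fact.** The documents do not support that. It needs several therapists and a therapist ICC above zero, and neither is given. The trial's therapist appears only in the singular, which proves nothing either way. The intervention is five fixed modules with written feedback, so a small ICC is plausible. At 0.01 with 10 therapists the power loss is under 2 points.

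**A reader might infer that the stated 80% power is too high.** That is not established either. The uncredited baseline adjustment could lift power above 80% even with therapist clustering. The sample size shows no allowance for drop-out, which the Discussion calls high for comparable interventions, and that works the other way. The net direction is unknown.

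**A reader might also take the 1.04 to cover centres.** It covers shifts only; centres enter through stratification and the model.

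**Blinding.** Therapist identifiers would exist only for treated patients, so a therapist term in the primary model would reveal allocation to an analyst who is meant to be blinded. This objection stands and shapes the remedy. It also cannot be assumed that the portal stores a usable therapist identifier: the article does not say so, and booklet users may not appear there.

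**Conclusion.** The concern holds conditionally. Therapist guidance is a possible source of correlation in the intervention arm alone, and neither the stated model nor the design effect carries it. Given several therapists and a positive therapist ICC, the standard error is too small and 103 per arm has less power than the same calculation without therapists.

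For 5 to 10 therapists and ICCs of 0.01 to 0.05, the loss runs from about 2 to about 16 percentage points of power, and the type I error from about 5.5% to 10.6%. These figures rest on assumed therapist numbers, equal caseloads and assumed ICCs. With ICC zero the plan's figures stand unchanged. With a single therapist the question becomes whether the result generalises beyond that person, and a random effect could not be estimated.

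The sample size calculation contains no arithmetical error.

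**What to change.** 1. Record the therapist of every treated patient, including those using the printed booklet.
2. Prespecify a partially nested version of the planned model: the same shift, centre and baseline terms, plus a random therapist effect in the intervention arm only, with small-sample degrees of freedom.
3. Run it as a key sensitivity analysis after the blinded primary analysis, or have an unblinded statistician run it, so that the stated blinding is kept.
4. With fewer than about 5 therapists, fix the therapist ICC at values from 0.01 to 0.05 instead of estimating it. With one therapist, state that the treatment effect cannot be separated from that person.
5. Report the number of therapists and the estimated therapist ICC.
6. In the sample size statement, say that the 80% power assumes no therapist clustering and put the range beside it.

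The cost is one recorded variable, one extra model and a more guarded power statement; no additional patients or staff are needed. The drawback is an imprecise estimate of the therapist variance when therapists are few.

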### Trial inclusion criteria

Chronic, adult dialysis patients, defined as being (i) 18 years or older and (ii) > 90 days on dialysis treatment, who are (iii) able to fill in a questionnaire in Dutch and have (iii) a depressive symptoms score of 10 or higher on the Beck Depression Inventory – second edition (BDI-II) [31], will be randomized to the intervention or control arm. This cut-off value of 10 showed promising results in earlier feasibility trials [21, 23].

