#### Primary outcomes

Depressive symptoms are assessed using a self-questionnaire, the BDI-II [33, 34]. Respondents are asked to rate how much each of these symptoms bothered them in the past week, on a scale ranging from 0 (not at all) tot 3 (severely). The total score has a minimum of 0 and a maximum of 63. Treatment response will be based on the change in depressive symptoms defined by a change in the sum score of the BDI-II. The BDI-II has been validated and extensively used in the dialysis setting [2, 31, 35]. Furthermore, the Quick Inventory of Depressive Symptomatology (QIDS-SR16) self-report questionnaire will be used to assess the specific depressive symptoms, its severity and its symptom domains [36].

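### The primary BDI-II model could also adjust for the baseline QIDS-SR16 that is already collected: an optional, modest gain in precision

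*Protocol article*

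**What the plan says.** The Statistical analysis section of the protocol article assesses change in depressive symptoms and in the other continuous outcomes with mixed models "with the respective clusters, centres and baseline scores as covariates". No scale is named. The natural reading is that each outcome is adjusted for its own baseline, so the BDI-II for its T0 score.

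The T0 BDI-II also decides entry: patients with "a depressive symptoms score of 10 or higher on the Beck Depression Inventory" are randomised (Trial inclusion criteria), and randomisation follows the T0 measurements (Randomization).

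Table 1 schedules the QIDS-SR16 at T0 and at every later assessment. The Primary outcomes section adds that this "self-report questionnaire will be used to assess the specific depressive symptoms, its severity and its symptom domains". It is thus measured before randomisation and plays no part in selection, but it is not named as a covariate for the BDI-II.

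On power, the Sample size section states "The power calculation is based on the comparison between T1 to T0 between the intervention and the control group", with d = 0.4, power 0.80 and alpha 0.05. It gives 99 per arm, then applies a design effect of 1.04 to reach 206 in total.

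**The concern.** A patient's single T0 BDI-II score is an imperfect reading of true severity at that moment. A second scale aimed at the same construct, completed at the same assessment, carries some information on true severity that the first misses. A model that uses only the first leaves that information in the residual.

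What is at stake is the standard error of the arm difference at T1, not its validity. The calculation lands almost exactly on 80% power and shows no step for attrition, so a gain that needs no new data deserves a look.

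**Working it through.** **1. The plan's own figure.** Two-sided alpha 0.05, power 0.80, d = 0.4, normal approximation: n = 2(1.960 + 0.842)²/0.4² = 98.1, rounded up to 99 per arm. Then 99 × 1.04 = 102.96, so 103 per arm and 206 in total. The stated figures reproduce. The effective number per arm is 103/1.04 = 99.04, and power = Φ(0.4·√(99.04/2) − 1.960) = Φ(0.855) = 0.804.

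**2. Model for the gain.** The article gives no correlations, so these inputs are assumptions: BDI-II reliability r1 = 0.75 to 0.90, QIDS-SR16 reliability r2 = 0.75 to 0.85, true-score stability from T0 to T1 s = 0.70 to 0.85. With one common true score and independent errors:

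- corr(T0 BDI-II, T1 BDI-II) = r1·s
- corr(T0 QIDS, T1 BDI-II) = s·√(r1·r2)
- corr(T0 BDI-II, T0 QIDS) = √(r1·r2)

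The proportional fall in residual variance is the squared partial correlation of T0 QIDS with T1 BDI-II, given T0 BDI-II:

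R = r1·r2·s²·(1 − r1)² / [(1 − r1·r2)(1 − r1²·s²)]

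**3. Results if d = 0.4 is on the BDI-adjusted SD.** Power uses 99.04/(1 − R) patients per arm.

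| r1, r2, s | R | 206 × R | Power |
|---|---|---|---|
| 0.90, 0.75, 0.70 | 0.00331/0.1960 = 1.7% | 3.5 | 0.810 |
| 0.85, 0.80, 0.78 | 0.00931/0.1793 = 5.2% | 10.7 | 0.824 |
| 0.75, 0.85, 0.85 | 0.02879/0.2152 = 13.4% | 27.6 | 0.856 |

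**4. Does the cut at 10 produce the gain?** No. The factor (1 − r1)² comes from measurement error in the BDI-II, and no term describes selection. Selecting on the T0 BDI-II leaves the distribution of the other scores given that score unchanged. At r1 = r2 = s = 0.8 the formula gives 7.7%, and simulation gave 7.6% whether the top 60% or the top 40% on the BDI-II were kept. Selection only lowers the share of T1 variance that the BDI-II itself explains.

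**5. If d = 0.4 is on the raw T1 SD.** Suppose (assumption) the top 60% are selected. The variance of the T0 BDI-II then shrinks by a factor k = 0.422 (truncated normal), and the BDI-II explains k·b²/(k·b² + 1 − b²) of T1 variance, with b = r1·s.

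- Largest-gain corner: b² = 0.406, explained share 0.224, power 0.892. With QIDS-SR16: 1 − 0.776 × 0.866 = 0.328, power 0.930. Gain 3.8 points.
- Smallest-gain corner: b² = 0.397, explained share 0.217, power 0.889. With QIDS-SR16: 1 − 0.783 × 0.983 = 0.231, power 0.894. Gain 0.5 points.

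**6. Relaxing the ideal model**, in the middle row of the table. Let the two T0 errors correlate c and the true scores of the two scales correlate ρ. Then corr(T0 BDI-II, T0 QIDS) = ρ·√(r1·r2) + c·√((1 − r1)(1 − r2)), and corr(T0 QIDS, T1 BDI-II) = ρ·s·√(r1·r2).

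| c | ρ | R | Power (adjusted SD) |
|---|---|---|---|
| 0 | 1 | 5.2% | 0.824 |
| 0.5 | 1 | 1.6% | 0.810 |
| 0 | 0.85 | 2.4% | 0.813 |
| 0.5 | 0.85 | 0.3% | 0.805 |

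**7. Against attrition.** With an assumed 20% loss and d on the adjusted SD, 99.04 × 0.8 = 79.2 per arm gives power 0.711. The middle-row gain raises it to 0.734 and the largest to 0.772. Both stay below 0.80.

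**The case against.** The strongest reply is that there is no error here. Adjusting an outcome for its own baseline, cluster and centre is standard. Regression to the mean after selection affects both randomised arms alike, so a reader who infers bias from the entry cut-off goes beyond the documents. A condensed article may also leave the final covariate list to a fuller plan. All of this stands. What remains is that the article does state a covariate set, and a collected prognostic score is not visibly in it.

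Other stronger readings also fail:

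- **That the model adjusts only for the BDI-II.** The text names no scale and does not rule out further covariates. Own-baseline adjustment is the natural reading, not a stated restriction.
- **That the truncated BDI-II makes the QIDS-SR16 valuable.** Step 4 shows that the proportional gain does not depend on the cut.
- **That the trial has no margin.** This is right for attrition, since 206 includes no allowance although the Discussion notes high drop-out in other populations. For precision it depends on the SD behind "We took the conservative small to medium effect size", which the article does not define. On the raw SD, baseline BDI-II adjustment already gives margin that the calculation did not count.

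The size is also open to attack. Both scales are self-reports in the same T0 assessment, so shared error is plausible, and they are different instruments. Step 6 shows that the gain can then almost vanish. This stands and sets the lower end of the range.

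**Conclusion.** The point holds as an optional improvement. Adding the T0 QIDS-SR16 to the primary BDI-II model is expected to reduce residual variance by about 2% to 13% under independent errors and the assumed reliabilities and stability, and by under 2% or almost nothing if errors are shared or true scores differ. In power this is roughly 0 to 5 points if d = 0.4 refers to the BDI-adjusted SD, and less if it refers to the raw SD. Every input apart from the sample-size figures is an assumption.

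The planned analysis is valid without the change, and the estimand and type I error are untouched. The gain would not make up for a 20% loss if d is on the adjusted SD, so it should not be offered in place of an attrition allowance.

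**What to change.** In the Statistical analysis section, or in the analysis plan before unblinding, name the T0 BDI-II and T0 QIDS-SR16 total scores as fixed covariates of the primary BDI-II model, beside centre and shift cluster. Add the T0 BDI-II to the QIDS-SR16 model in the same way. State a simple baseline imputation for a missing T0 score, so that no patient is lost through the added covariate. It would also help to say which SD d = 0.4 refers to.

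The cost is one degree of freedom per model and a sentence of text, with no new data. Recruitment was open when the article was submitted and analysts are to stay blinded until the primary analysis, so the change can be prespecified cleanly. If both baseline scores were intended all along, naming them settles the point.
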